### Trial design {8}

The overall effect of the intervention is estimated using a two-arm, parallel group, longitudinal, pair-matched cluster-randomised controlled superiority trial design. Clusters are defined as villages with 10–75 eligible households, within which households act as the observational unit (see ‘Eligibility criteria {10}’ section for further details).

The DIG programme has identified more than 11,000 eligible households, but only has funding to reach 2700 households under the programme. Randomisation is therefore an equitable way to select households for inclusion. It is also not yet clear that the intervention is effective for people with disabilities and their families. Cluster randomisation was chosen in part because of the nature of the DIG programme, which includes components delivered at the village level.

After random allocation of villages into intervention and control arms, but prior to implementation of the intervention, a baseline survey at household level is conducted (November 2020). The DIG programme is then implemented for 18 months from December 2020 to June 2022. Two endline household surveys are undertaken—the first in July 2022 for participants with a disability to determine the effects of DIG at programme end (endline 1); and a second one in October 2023 for all participants (endline 2), inclusive of participants with disabilities, to assess the longer-term differential effects of the DIG programme between households with and without disabilities.

This work is complemented by a process evaluation to further understand implementation of the DIG programme. The process evaluation is guided by theoretical considerations, such as What underlying theory are we testing with this intervention? What is the theory underlying the design of the graduation programme? And what is the theory underlying the adaptations to make them inclusive? These considerations ground the process evaluation in the relevant wider literature, and support generalisability to future intervention designs that draw on similar theories. To facilitate consideration of theory, an unambiguous articulation of project theory as supposed by the delivery team is developed iteratively in the form of a directed acyclic graph (DAG), based on the theory of change and using set rules for specifying how change is expected to happen.

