Available data from the screening and verification visits informed the estimated total number of clusters that would be needed to reach 5400 eligible households. During the screening and verification process, BRAC Uganda found that approximately 25% of project participants were people with disabilities, and as such it was expected that the trial would include 675 people with disabilities in each arm. The distribution of eligible households per village was used to simulate the trial, 185 villages sampled with replacement from the verified villages gave approximately 5400 research participants in a simulated trial. A value of 0.8 was used from a recent evaluation of the graduation programme in Ghana for the standard deviation of the distribution of the normalised per-capita expenditure at baseline [10]. Since the degree of clustering in the outcome was unknown, the intraclass correlation coefficient (ICC) was allowed to vary between 0.05 and 0.3. The estimated between-village variation in mean level of the outcome at baseline and individual-level outcomes were drawn from the village-level means with a constant within-village variance. The endline results were generated using the simulated baseline data and a covariance matrix with a pre-post correlation of either 0.4, 0.6, or 0.8. The 185 clusters were pair-matched by the number of people with disabilities and a constant intervention effect was applied to the clusters allocated to the intervention arm. The intervention effects ranged from a difference between the intervention and control arms in the mean per-capita expenditure of zero standard deviations of the baseline per-capita expenditure, to 0.2 standard deviations, which is as high as the largest effects on per-capita expenditure observed in previous trials [1]. Multi-level linear regression was used to estimate the effects, controlling for baseline per-capita expenditure, accounting for clustering with a village-level random effect, and for the randomised design with fixed-effect for the pairs.

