## Assignment of interventions: allocation

### Sequence generation {16a}

Randomisation is stratified by BRAC office branch, to ensure sufficient programmatic support to the clusters in the intervention arm, and pair-matched based on the number of people with disabilities. For each branch, clusters are ranked by the number of project participants who are people with disabilities. Adjacent clusters in the ranked lists are paired. Each cluster in a pair is randomly allocated to each arm using random number allocation in using Stata (StataCorp. College Station, TX: StataCorp LLC).

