## Statistical methods

### Statistical methods for primary and secondary outcomes {20a}

For basic description, we will report the mean and standard deviation (or median and interquartile range) for continuous variable and the number and percentage for categorical variables, by intervention status (yes or no), and by data wave (baseline vs follow-up). We will test the balance of the covariates by *t*-test (or Mann Whitney *U* test) for continuous variables and by chi-square test for any categorical variables. Covariates include socio-demographic factors (e.g., age, sex), as well as any other factors likely to affect the implementation of the intervention.

Data will be fitted with multi-level linear regression to test the effect of the intervention, with the difference of the primary or secondary outcomes between follow-up and baseline as the outcome, and intervention status as the exposure, controlling for potential imbalance in covariates at baseline. To account for the data structure, we will consider the random intercept and random slope for exposure at the level of district and pair indicators. To address multiplicity concerns the Bonferroni Correction or Bayesian modelling approaches will be applied. The model’s adequacy will be assessed through residual plots, with log transformations of variables considered if residuals are not randomly distributed. All analysis will be conducted in Stata and R. We will report the estimation as coefficient for continuous outcome and OR for binary outcome, as well as their 95% confidence interval (CI). *P* value < 0.05 will the level of statistical significance.

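### Baseline balance is tested without allowance for clustering and adjustment is tied to imbalance, while the baseline outcome covariate and pair fixed effects assumed in the sample-size work are not fixed in the model

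*Protocol article*

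**What the plan says.** Trial design {8} describes a "pair-matched cluster-randomised controlled superiority trial design". Under Sequence generation {16a}, randomisation is stratified by BRAC branch and "pair-matched based on the number of people with disabilities". Implementation {16c} reports 96 intervention and 89 control clusters, with 2898 and 2402 households.

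The first paragraph of the statistical methods section {20a} states: "We will test the balance of the covariates by" t-test or Mann-Whitney U test for continuous variables and "by chi-square test for any categorical variables". No cluster or pair term is attached to these tests. The covariates are given by example (age, sex) and then left open: "as well as any other factors likely to affect the implementation of the intervention".

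The second paragraph sets the model for primary and secondary outcomes. It is a multi-level linear regression of the follow-up minus baseline difference on arm, "controlling for potential imbalance in covariates at baseline". Random intercepts and slopes at district and pair level are to be considered. The only threshold in the section is that a P "value < 0.05 will the level of statistical significance".

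The simulation under Sample size {14} used a different, fixed model: baseline per-capita expenditure as a covariate, a village random effect, and fixed effects for the pairs.

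**The concern.** There are three linked problems.

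- **The tests do not fit the design.** With villages randomised, households in the same cluster are not independent. Ordinary two-sample tests understate the variance of the difference between arms, so their p-values are too small. Under randomisation any baseline difference is a chance difference in any case, so even a valid test would say little.
- **Adjustment is tied to imbalance and the set is not fixed.** The tests are the only tool the section gives for judging imbalance, so they will probably inform which covariates enter. The set could then differ between endline 1 (disability households only) and endline 2 (everyone), in an unblinded evaluation.
- **The effect model departs from the one behind the precision claim.** A change score without the baseline value as a covariate is less precise than the baseline-adjusted model that was simulated.

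At stake are misleading balance p-values, avoidable analytic freedom in the primary model, and lost precision.

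**Working it through.** **Inputs from the protocol article.** Clusters: 96 + 89 = 185. Households: 2898 + 2402 = 5300. Expected participants with disabilities: 0.25 × 2700 = 675 per arm, which reproduces the figure in Sample size {14}, so 1350 in total. Nominal level 0.05, taken as two-sided. ICC: "the intraclass correlation coefficient (ICC) was allowed to vary between 0.05 and 0.3"; this range is for the outcome. Pre-post correlation r: 0.4, 0.6 or 0.8.

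**Assumptions.** No covariate ICC is given. I use the outcome range for strongly clustered covariates and 0.005 to 0.03 for weakly clustered ones such as age or sex. Pairing is ignored; it would lower the rates for covariates related to the number of people with disabilities.

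**Step 1: chance-flag rate of a test that ignores clustering.**

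Mean cluster size m: 5300/185 = 28.6 (full sample) and 1350/185 = 7.3 (participants with disabilities). Design effect DE = 1 + (m − 1) × ICC. Actual rejection rate = 2 × [1 − Φ(1.96/√DE)].

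| ICC | DE, m = 28.6 | Rate | DE, m = 7.3 | Rate |
|---|---|---|---|---|
| 0.005 | 1.14 | 6.6% | 1.03 | 5.4% |
| 0.03 | 1.83 | 14.7% | 1.19 | 7.2% |
| 0.05 | 2.38 | 20.4% | 1.31 | 8.7% |
| 0.10 | 3.76 | 31.2% | 1.63 | 12.5% |
| 0.30 | 9.29 | 52.0% | 2.89 | 24.9% |

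Example: m = 28.6, ICC = 0.05 gives √2.38 = 1.54, 1.96/1.54 = 1.27, and a two-sided tail of 0.204.

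Simulated naive t-tests on 185 clusters of unequal size (96 v 89, 4000 runs) gave 24.5%, 36.8% and 58.2% at ICC 0.05, 0.10 and 0.30 in the full sample, and 9.4%, 14.2% and 30.9% among participants with disabilities. At ICC 0 they gave 5.0% and 5.3%, so the simulation is calibrated.

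The number of covariates is not stated. With 10 assumed, the full-sample formula at ICC 0.05 to 0.3 gives about 2.0 to 5.2 flagged by chance, against 10 × 0.05 = 0.5 for valid tests.

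**Step 2: does selection by these tests disturb the treatment test?**

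A cluster-level analysis was simulated with 184 equal clusters of 29 households, 10 covariates each weakly related to the outcome, ICC 0.01 to 0.3, and 1500 runs per setting. Type I error was 4.1% to 4.7% with test-selected covariates and 3.5% to 4.9% with a fixed set. The Monte Carlo standard error near 5% is √(0.05 × 0.95/1500) = 0.6 percentage points. There is no sign of inflation.

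**Step 3: change score against baseline adjustment.**

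Assume outcome variance σ² at both waves and the same r within and between clusters. The change score has variance 2σ²(1 − r); the baseline-adjusted outcome has σ²(1 − r²). The ratio is 2(1 − r)/(1 − r²) = 2/(1 + r).

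- r = 0.4: 2/1.4 = 1.43, or 43% larger
- r = 0.6: 2/1.6 = 1.25, or 25% larger
- r = 0.8: 2/1.8 = 1.11, or 11% larger

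**The case against.** The tests stand in a paragraph introduced as basic description. The modelling sentence speaks of potential imbalance, sets no threshold and does not refer back to the tests. The covariate list is something an analysis plan commonly settles. And the high flag rates borrow an ICC that belongs to expenditure.

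Much of this stands, and it rules out several stronger readings:

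- **That covariates enter by significance test as a stated rule.** The article does not say so. It is the natural inference and no more.
- **That the baseline outcome, branch and number of participants with disabilities enter only if they look imbalanced.** The change score always uses the baseline value. Pairs are formed within branch by ranking on that number, and pair-level random terms are at least to be considered. Neither depends on a balance test.
- **That the primary type I error is inflated.** The simulation shows none.
- **That false imbalances will be reported as failed randomisation, or that the set will vary by outcome.** Nothing says the first. Tests of baseline covariates by arm do not depend on which outcome is modelled, so at most the set differs between endlines.
- **That 20% to 52% is the expected rate.** It holds only for covariates as clustered as the outcome is assumed to be. For age and sex the rate may be close to nominal, above all among participants with disabilities, on whom the sample size rests.

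The objection does not remove the point. Tests without allowance for clustering are a method the article states, not a detail left to another document, and so is an effect model that differs from the simulated one.

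**Conclusion.** The point holds in a limited form and should be corrected. The balance tests do not suit a cluster-randomised design. Their chance-flag rate runs from barely above nominal (about 5% to 7% among participants with disabilities, 7% to 15% in the full sample, at assumed ICC 0.005 to 0.03) to far above it (9% to 25% and 20% to 52%) if covariates share the outcome's assumed ICC of 0.05 to 0.3. Tying adjustment to imbalance leaves the primary model open to dependence on the data; this rests on the natural reading of the section. The cost shown is in credibility and precision, not in type I error. Leaving out the baseline covariate raises the variance by about 11% to 43% over the protocol's own correlations, given equal variances at both waves and one correlation at both levels.

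**What to change.** 1. Delete the baseline significance tests. Describe baseline by arm, with standardised differences if wanted.
2. Fix the adjustment set in advance for every outcome: the baseline value of that outcome where it was collected; the pair terms used in the sample-size simulation, or branch and the cluster's number of participants with disabilities; and a short named list such as age and sex. The alternative to pair terms matters because, with 96 and 89 clusters, at least 96 − 89 = 7 intervention clusters can have no one-to-one partner.
3. The change score may stay as the dependent variable. In a linear model, adding the baseline value as a covariate gives the same treatment estimate as modelling the follow-up value with that covariate.
4. Label any further adjustment for observed imbalance as a sensitivity analysis.

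The cost is a change of wording in the statistical methods section and a rule for missing baseline values. No new data are needed.

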### Eligibility criteria {10}

For the purposes of intervention delivery and evaluation, clusters are villages with 10–75 eligible households. This cluster size is necessary for the Village Savings and Loans Associations (VSLAs) and Village Poverty Reduction Committees (VPRCs) (described further under *Intervention description*). To create a cluster, either nearby small villages are grouped or larger villages split to create a manageable cluster, that is, having between 10 and 75 eligible households. For small villages, the geographic distance from its centroid was calculated to the centroid of its adjacent villages, using eligible household’s GPS coordinates. The village concerned was then grouped with adjacent villages having the shortest distance. To split larger villages, we relied on *k*-means clustering to iteratively group neighbouring households, using their GPS coordinates, within a village into clusters. From the 156 villages identified near the BRAC Uganda branch offices in the target districts as potential sites for the DIG programme, 185 of these artificial clusters were created, each with at least 10 eligible households.

Identification of eligible households is based on household-level data collected by the implementing partners (BRAC, HI, and NUWODU). Households are eligible if they meet at least three out of five criterions, as this was felt to be an adequate threshold and would also reflect variations in household experiences of poverty. That is, (1) having a person with disability, (2) being a female-headed household or dependent on earnings from a female member of the household, (3) having children who are out of school, (4) poor housing conditions (floor, roof, and wall), and (5) low productive asset endowment. The Washington Group short set of questions is used to identify households with people with disabilities, based on those that report ‘a lot’ of difficulty on at least one dimension of the six-question set (i.e. walking, seeing, hearing, communicating, understanding and self-care) [8]. Ultra-poor households without a person with disabilities are still eligible for inclusion in the DIG programme in order to ensure there are enough households within each cluster for village-level interventions to operate.

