### Implementation {16c}

Assignment of clusters to intervention and control arms is led by the implementing partners (BRAC, HI, and NUWODU) with support from IERC and BIGD, in order to meet the criteria for the evaluation. Allocation is conducted at one time point prior to the baseline survey and implementation of the DIG programme. The programme team pre-identified the desired number of intervention beneficiary households that each of the eight BRAC branches could support based on the sample size of 2700 households. This number ranged from 320 to 420 households.^1^ The number of eligible households, identified during the screening and verification process, within each cluster was calculated. Permutations of cluster allocation were then run in Stata, until the desired total number of 2700 households for the DIG programme was reached in the intervention arm. Remaining clusters were assigned to the control. In the end, 96 clusters were assigned to the intervention arm and the remaining 89 clusters to the control arm. Overall, 2898 households were assigned to the intervention arm while 2402 households were retained as control—the distribution of households by district and BRAC branch is shown in Table 2.

**Table 2 Tab2:** Distribution of households in control and intervention arms by district and BRAC branch

District	BRAC Branch	Number of Households		
		Control Arm	Intervention Arm	Total
Gulu	Gulu	367	355	722
	Lacor	288	340	628
	Goma	280	406	686
Nwoya	Anaka	366	370	736
Oyam	Minakulu	324	402	726
	Kamdini	285	357	642
	Loro	263	311	574
Kiryandongo	Kigumba	229	357	586
Total		2402	2898	5300

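### The analysis model names no random effect for the randomised cluster and conflicts with the model behind the precision claim; error control then depends on a pair-level slope that is only to be considered

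*Protocol article*

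**What the plan says.** **Analysis model.** Statistical methods {20a} specifies multi-level linear regression "with the difference of the primary or secondary outcomes between follow-up and baseline as the outcome", with intervention status as the exposure. For the data structure it says "we will consider the random intercept and random slope for exposure at the level of district and pair indicators". No village or cluster term is named.

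**Randomised unit and stratum.** Sequence generation {16a} says "Randomisation is stratified by BRAC office branch" and "For each branch, clusters are ranked by the number of project participants who are people with disabilities". Neighbours in the ranked list form a pair, and "Each cluster in a pair is randomly allocated to each arm using random number allocation". The randomised unit is therefore the cluster, the stratum is the branch (8 in Table 2), and pairs lie within branches. District has 4 levels and is neither the randomised unit nor the stratum.

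**Allocation achieved.** Implementation {16c} reports that "96 clusters were assigned to the intervention arm and the remaining 89 clusters to the control arm".

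**Model behind the precision claim.** Sample size {14} describes a regression that controls for baseline expenditure, "accounting for clustering with a village-level random effect, and for the randomised design with fixed-effect for the pairs".

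**What a cluster is.** Under Eligibility criteria {10}, "either nearby small villages are grouped or larger villages split to create a manageable cluster". In this way 156 villages became 185 clusters.

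**The concern.** In a cluster-randomised trial the variance between randomised units drives the standard error of the treatment effect. If the model does not carry that variance, intervals are too narrow and the type I error exceeds its nominal level. Here the one sentence on data structure leaves the randomised unit unnamed, makes the terms it does name discretionary, and departs from the model used to justify the study's precision. Models with quite different error rates would all comply with it. Allocation is unmasked, and the first endline had been collected when the article was written, so a choice of variance terms made after seeing results could decide whether p falls below 0.05.

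**Working it through.** The plan states no type I error or standard error to reproduce, so the check starts from its inputs.

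**1. Inputs**
- Clusters: 96 + 89 = 185. Households: 2898 + 2402 = 5300, so 5300/185 = 28.6 per cluster.
- Participants with disabilities: 25% of 2700 = 675 per arm, which reproduces the protocol's figure; 1350/185 = 7.3 per cluster.
- ICC: 0.05 to 0.30 (Sample size {14}). The protocol uses this range for expenditure. It gives no ICC for the change score, so applying the range to the change score is an assumption.

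**2. Pairing.** A pair with one cluster per arm uses one control cluster. At most 89 such pairs exist, and at least 96 − 89 = 7 clusters lie outside them.

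**3. When a pair slope replaces a cluster effect.** Let each cluster have an independent effect with variance t². In an intact pair, write the control cluster's effect as a and the intervention cluster's as a + b. Then Var(a) = t², Var(b) = 2t² and Cov(a, b) = −t². A random intercept and slope by pair can reproduce this only if the covariance is free. An independent structure forces it to zero.

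**4. Pair intercept only, closed form.** Take P = 92 balanced pairs, m participants per cluster, total variance 1, between-cluster variance s2c = ICC and within-cluster variance s2w = 1 − ICC.
- The true variance of the effect is proportional to T = s2w + m·s2c.
- The model uses the pooled residual R = [(P−1)·T + 2P(m−1)·s2w] / [(P−1) + 2P(m−1)].
- Type I error = 2Φ(−1.96/√(T/R)).

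| m | ICC | T | R | T/R | Type I error |
|---|---|---|---|---|---|
| 7.3 | 0.05 | 1.315 | 0.977 | 1.35 | 9.1% |
| 7.3 | 0.30 | 2.890 | 0.859 | 3.36 | 28.5% |
| 28.6 | 0.05 | 2.380 | 0.975 | 2.44 | 21.0% |
| 28.6 | 0.30 | 9.280 | 0.851 | 10.9 | 55.3% |

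**5. Simulation under no effect.** 400 runs per scenario, 185 clusters split 96 v 89, m = 28.6, ICC 0.05 or 0.30, and 0% or 30% of between-cluster variance shared within pairs. Two layouts were used: 89 intact pairs plus 7 single clusters, and allocation that ignored the pairs. District effects were not simulated.

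| Random effects fitted | Model SE / true SE | Type I error |
|---|---|---|
| Pair intercept only, ICC 0.05 | 0.66–0.77 | 12–21% |
| Pair intercept only, ICC 0.30 | 0.32–0.36 | 48–56% |
| Pair intercept + slope, independent | 0.84–0.92 | 7–13% |
| Pair intercept + slope, unstructured | 0.96–1.01 | 5–7% |
| Pair + explicit cluster | 0.95–1.00 | 4.8–6.5% |

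Monte Carlo error is about 1 percentage point near 5%. A smaller simulation (200 runs per scenario, both cluster sizes) gave 3.5–8.5% with the unstructured slope and 9.5–61.5% with the pair intercept only.

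**6. Sensitivity to the ICC assumption.** With the formula in step 4, a change-score ICC of 0.01 gives 5.8% (m = 7.3) and about 8.4% (m = 28.6). An ICC of 0.02 gives 6.6% and about 11.8%.

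**The case against.** The strongest reply is that the plan does list a random slope for exposure by pair. With one cluster of each pair in each arm, pair-by-exposure identifies the cluster, and the model as listed behaves much like an explicit cluster model if the covariance is unstructured. That stands. A reader might infer that standard errors under the plan are far too small. The document does not support this, because the large figures belong to a model with the slope dropped. The verb *consider* governs intercept and slope alike, so the text neither secures the slope nor singles it out for omission.

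The imperfect pairing does little harm by itself: the unstructured slope held up in both simulated layouts. The 96 v 89 split shows only that pairing cannot be wholly 1:1. The document does not say how many pairs stayed intact.

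The ICC objection also stands. Stable differences between villages cancel in a change score, so the relevant ICC may lie below 0.05 and the inflation may be smaller, as step 6 shows.

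A reader might also infer that leaving out branch shrinks the standard errors. It does not follow: pairs lie within branches, so pair terms already carry branch differences, and omitting a stratum effect does not usually reduce the standard error. A district random slope would tend to widen intervals, not narrow them.

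Covariance structure and degrees of freedom are details an article may leave to a fuller document. The conflict between two stated models, and the unnamed randomised unit, are in the text itself.

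**Conclusion.** The point holds in conditional form. Statistical methods {20a} names no effect for the randomised cluster, makes its random effects discretionary, and disagrees with Sample size {14} on how clustering is handled. The plan as worded therefore admits models with type I error from about 5% (unstructured pair slope, or explicit cluster term), through 7–13% (independent slope), to 9–29% for participants with disabilities and 21–55% for all households (pair intercept alone).

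These ranges rest on the protocol's ICC range holding for the change score, equal cluster sizes and, in the simulations, no district effects. The independent-slope range was computed at 28.6 per cluster only. The finding is that the model is not fixed on its main variance component; it is not that the listed model necessarily fails.

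**What to change.** Replace the sentence on data structure in Statistical methods {20a} with text to this effect:

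> Every model for a primary or secondary outcome includes a random intercept for the randomised cluster. Pair effects are included where a pair was actually randomised 1:1. Branch effects are used for clusters outside such pairs, or in place of pair effects throughout. District random effects are not relied on to carry the clustering.

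Three points of detail:
- Fixed effects for pair and for branch should not both be fitted to the same clusters: pairs lie within branches, so the branch effects would be aliased.
- The term should be the randomised cluster, not the original village. Some clusters are parts of a split village and others are several villages grouped, so nesting every cluster in a village would not work.
- Sample size {14} and Statistical methods {20a} should then describe the same model, including whether the outcome is the change score or the follow-up value adjusted for baseline.

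The cost is a few sentences and no new data. Intervals may be somewhat wider than under a model without the cluster term. The wording should be settled before the models are run.

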**Methods:**

The DIG programme works with project participants over a period of 18 months. Participants receive unconditional cash transfers for 6 months, training, access to savings-and-loans groups, and a capital asset that forms the basis of their new livelihood. The programme is also adapted to address specific barriers that people with disabilities face. Eligible households are clustered by geographical proximity in order to deliver the intervention. Eligibility is based on household screening to identify the ‘ultra-poor’ based on proxy means testing—both households with and without people with disabilities are included in the programme. Clusters are randomly selected prior to implementation, resulting in 96 intervention and 89 control clusters. The primary outcome of the trial is per-capita household consumption. Before the start of the intervention, a baseline household survey is conducted (November 2020) among project participants and those not offered the programme, a similar endline survey is conducted with participants with disabilities at the end of programme implementation in July 2022, and a second endline survey for all participants in October 2023. These activities are complemented by a process evaluation to understand DIG programme implementation, mechanisms, and context using complementary qualitative and quantitative methods. Ethical approval for the research has been received from Mildmay Uganda Research Ethics Committee and London School of Hygiene and Tropical Medicine.

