## Methods: participants, interventions and outcomes

### Study setting {9}

Kiryandongo, Gulu, Nwoya, and Oyam districts in Uganda are the selected sites for DIG programme implementation. These districts are characterised by higher than national average levels of poverty, social deprivation, and prevalence of disability. A map of programme locations is shown in Fig. 1.

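### The optional district-level random slope for exposure rests on only four selected districts and would make the primary interval erratic and, on average, too wide

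*Protocol article*

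**What the plan says.** The section on statistical methods for primary and secondary outcomes {20a} plans a multi-level linear model for the change from baseline. On its random part it says "we will consider the random intercept and random slope for exposure at the level of district and pair indicators". It names no degrees-of-freedom method.

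Three other places bear on this sentence:

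- Study setting {9} lists four districts: "Kiryandongo, Gulu, Nwoya, and Oyam districts in Uganda are the selected sites for DIG programme implementation".
- Sequence generation {16a} gives the stratum as the branch: "Randomisation is stratified by BRAC office branch, to ensure sufficient programmatic support to the clusters in the intervention arm". Implementation {16c} refers to the households "that each of the eight BRAC branches could support". In Table 2 the branches are nested in districts: three in Gulu, one in Nwoya, three in Oyam and one in Kiryandongo.
- Sample size {14} describes a different model for the precision simulation, "accounting for clustering with a village-level random effect, and for the randomised design with fixed-effect for the pairs". In that simulation "a constant intervention effect was applied to the clusters allocated to the intervention arm".

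**The concern.** A random slope for exposure at district level treats the district effects as draws from a distribution and estimates the variance of that distribution. Here it has four draws, so at most 3 degrees of freedom. Such an estimate is often exactly zero. When it is not zero, it is added to the uncertainty of the treatment effect and can dominate it.

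The term matches nothing else in the design. District is not a randomisation stratum, and the four sites were not sampled from a larger set. The precision statement was derived with a constant effect and no district term, so it contains none of the variance this slope could add.

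At stake is the stability of the primary interval. Whether an effect near 0.1 SD reaches significance could turn on whether the software returns zero for one poorly determined variance. Precision is also lost for the question the trial can answer, which is the effect in the districts studied.

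**Working it through.** **The plan's own figure.** The document gives no figure for the district slope. The nearest is the statement that a true effect of 0.1 SD would be detected. A rough closed form uses 675 people with disabilities per arm, a mean cluster size of 1350/185 = 7.3, and SE = √[2(1 − ρ²)(1 + 6.3·ICC)/675] in SD units:

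- ρ = 0.4, ICC = 0.05: √(2 × 0.84 × 1.315/675) = 0.057, power 42%.
- ρ = 0.4, ICC = 0.3: √(2 × 0.84 × 2.89/675) = 0.085, power 22%.
- ρ = 0.8, ICC = 0.05: √(2 × 0.36 × 1.315/675) = 0.0375, power 76%.

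This does not reproduce the plan's statement under its conservative inputs. That statement came from a simulation whose results figure is not shown, and the present point does not depend on it. The closed form serves only to show that the SE values assumed below, 0.045 to 0.08, are plausible.

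**Inputs.**

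- Households by district, summed from Table 2: Gulu 2036, Nwoya 736, Oyam 1942, Kiryandongo 586; total N = 5300.
- SE without a district slope, SE₀: assumed, 0.045 or 0.08 SD.
- True between-district SD of the effect, τ: assumed, 0 to 0.15 SD.
- True mean effect: 0.1 SD.

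**Formulae.** The estimated effect in district d has sampling variance v_d = SE₀²·N/n_d. With a slope variance estimated by REML as τ̂², the weights are w_d = 1/(v_d + τ̂²) and SE = 1/√Σw_d. If τ̂² = 0, SE = SE₀ and the slope has no effect.

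**One case by hand.** Take SE₀ = 0.045. Then v_d = 0.00527 (Gulu), 0.01458 (Nwoya), 0.00553 (Oyam) and 0.01832 (Kiryandongo). If the software returns τ̂ = 0.10, the weights are 65.5, 40.7, 64.4 and 35.3, with sum 205.9, so SE = 0.070.

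- The SE is 1.55 times as large as without the slope.
- For an estimate of 0.1 SD, z falls from 0.1/0.045 = 2.22 to 0.1/0.070 = 1.43.
- Kiryandongo's weight rises from 586/5300 = 11% to 35.3/205.9 = 17%, so the estimate also moves away from the household-weighted average.

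**How poorly four values fix the variance.** A variance on 3 df has a 95% sampling range of 0.07 to 3.1 times its true value.

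**Simulation** (20,000 trials per row, normal 95% intervals, SE as a ratio to SE₀). In paired columns the first figure is with the slope and the second without.

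| SE₀ | τ | τ̂² = 0 | Mean SE ratio | 90th centile of SE ratio | Coverage %, four study districts | Coverage %, hypothetical district population | Power % |
|---|---|---|---|---|---|---|---|
| 0.045 | 0 | 63% | 1.14 | 1.53 | 96.2 / 94.9 | 96.2 / 94.9 | 51 / 60 |
| 0.045 | 0.10 | 32% | 1.49 | 2.26 | 97.8 / 95.1 | 89.5 / 78.5 | 36 / 57 |
| 0.045 | 0.15 | 18% | 1.86 | 2.90 | 98.6 / 94.8 | 86.8 / 64.8 | 30 / 58 |
| 0.08 | 0 | 63% | 1.15 | 1.54 | 96.3 / 95.1 | 96.3 / 95.1 | 18 / 23 |
| 0.08 | 0.10 | 49% | 1.26 | 1.81 | 97.0 / 95.0 | 92.9 / 88.9 | 20 / 29 |
| 0.08 | 0.15 | 38% | 1.40 | 2.09 | 97.5 / 94.9 | 90.6 / 82.2 | 19 / 32 |

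The clean power comparison is at τ = 0, where both analyses have the same target. The exact powers without the slope there are 60.3% and 24.0%. If a t reference on 3 df replaced the normal one, intervals would be a further 3.18/1.96 = 1.62 times as wide.

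**The case against.** The strongest objection is that the wording is only an option. A component estimated at zero, or one that fails to converge, could be dropped, and the sentence does not make clear which term belongs to district and which to pair. This stands in part: the slope is permitted, not fixed. But the section names the term, and leaving it open means that the standard error of the primary result depends on a choice that could be made with the data in view.

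A second objection is that the slope is often harmless. This is also partly right. In about 62 to 63% of trials without heterogeneity the model collapses to the one recommended here, and coverage is then about 96%, so false positives do not increase. It would therefore overstate the point to say that the standard error always rests on 3 degrees of freedom. It does so largely when the variance is estimated above zero.

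A reader might also infer that the interval is too narrow and undercovers. The documents do not support this for the effect in the study districts, where the slope interval covers 96-99% in every setting tried. Coverage of roughly 87-94% arises only for the mean of a hypothetical population of districts when τ is 0.10 to 0.15. For that target, leaving the slope out covers even less (64-90%). The two targets must not be mixed.

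Finally, the authors want results that inform other settings, so letting the effect vary by place is a reasonable aim. Four selected districts serve it poorly.

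**Conclusion.** The point holds as one of instability and lost precision. The optional district slope is estimated from four selected districts, matches neither the branch strata nor the precision model, and makes the width of the primary interval erratic.

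With no true district variation, the SE is about 15% larger on average and at least 50% larger in one trial in ten. Power at 0.1 SD falls from about 60% to 51% (SE₀ = 0.045) or from about 24% to 18-19% (SE₀ = 0.08). With true variation of 0.10 to 0.15 SD, the average SE is about 26% to 86% larger, but variation that large equals or exceeds the whole 0.1 SD effect and nothing in the document suggests it.

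The figures assume values for SE₀ and τ, a normal-based interval, REML estimation, and precision in each district proportional to its households in Table 2. The instability of a variance from four values does not depend on the exact values.

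**What to change.** In the statistical methods section {20a}:

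- Delete the random intercept and the random slope for exposure at district level.
- Handle geography by fixed effects for branch, which absorb district because branches are nested in districts, or for the matched pairs as in the sample size section. With "resulting in 96 intervention and 89 control clusters", at least 96 − 89 = 7 intervention clusters have no control partner. Under pair fixed effects an unpaired cluster adds nothing to the effect estimate, so the choice should be stated.
- Keep a random effect at cluster (village) level. Only the district terms should go, because clustering must still be accounted for.
- Report district-specific effects in a descriptive table or through an arm-by-district test.

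This is a change of wording and brings the analysis into line with the randomisation and the precision model. It should be made before outcomes are compared by arm. The cost is that the inference is stated for the four study districts and does not cover variation to other districts, which four districts could not reliably support.
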